## 3. Statistical Analysis

### 3.1. Sample Size

#### 3.1.1. Test of Superiority (Primary Endpoint) for G1 versus G2 Comparison

For an allocation 1 : 2 to test the percentage of bone consolidation between G1 and G2, the sample size of 36 in comparator arm (ICA) and 72 in experimental arm (hBM-MSC) achieve more than 80% power to detect superiority with a clinically meaningful margin of superiority of 20%, considering a 5% loss. Despite the uncertainties derived from the fact that no head-to-head comparisons have been tested in well-designed randomized clinical trials, literature data suggest that the control arm (G1) may have a rate of 74% in efficacy [8] and that it is reasonable to expect 20% superiority for the rate of responders in the experimental arm (G2a + G2b) [21, 22]. The significance level of the test will be established at the 2.5% one-sided alpha level (equivalent to 5% two-sided alpha level).

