### 3.2. Plan of Analysis

Primary and secondary endpoints and the statistical plan of analysis are described in Table 1. Five subgroups for analysis are declared: manufacturing site (Spain, France S1, France S2, Germany, and Italy); anatomical site: femur, humerus, and tibia; time (months) since acute fracture; smoking habits (yes/no); and sex (female/male). For these, Fisher's exact test for categorical variables, *t*-test or one-way ANOVA for Gaussian distributed variables, Mann–Whitney test and Kruskal-Wallis for non-Gaussian continuous variables will be used.

The plan of analysis will be tested in the following two populations of analysis: (a) modified full analysis set (mFAS) that will include all patients who have received treatment; (b) per protocol population (PP) that will include those patients in the mFAS set without major protocol deviations. Procedures to account for missing or spurious data will include patients whose information on consolidation is unknown at the end of the trial and will be considered failures, irrespectively, to the drop-out reason. With regard to the radiological consolidation, the baseline value will be used to impute the missing case; in case of treatment-related missing data, the missing case is not imputed otherwise. No formal imputations will be performed for the rest of variables, and the analyses will be based on the Available Data Only (ADO) approach.

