## 4. Discussion

There is a lack of multicentric, randomized clinical trials in the literature, capable of defining the value of current regenerative medicine strategies based on MSCs. Bone healing in difficult clinical settings has gathered multiple early trials with cell therapy, but the available evidence is limited.

Nonunions after long bone fractures are a challenging scenario to evaluate the efficacy of cell therapy or other competing technologies. Furthermore, the severity of the included cases may impact the results. Delayed unions of the tibia were healed by bone marrow MSCs and platelet-rich plasma [25], but obviously the severity of the cases was limited. Clinical trials on the treatment of long nonunions frequently include any type of nonunion, from hypertrophic to oligotrophic or atrophic, and the results may be impacted by the case mix. A reference multicentric trial [8] included 25% atrophic nonunions in the control arm versus 42% in the experimental arm. To solve this issue, our trial will exclude hypertrophic nonunions.

The control arm in comparative trials about bone healing is a difficult choice. Although iliac crest autograft has long been considered the standard augmentation to obtain bone healing, this control may be variable due to the patient and the surgical variability. Besides, no reference studies are available about the effectiveness of ICA to support bone healing in nonunions. Recent data can only be obtained from its use as controls in other studies [8, 26], but the variability in the obtention of ICA and the subsequent complications [7, 27, 28] foster the proposal of alternatives. We used this information to quantitatively estimate the expected healing rates with ICA, although it may vary depending on the type and location of the nonunion.

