**Figure 2 fig2:**
[figure not shown]
Flow diagram of the ORTHOUNION clinical trial.

**Table 1 tab1:** Outcome measure and statistical analysis table.

Objective	Outcome measure	Time points of evaluation	Statistical analysis
Principal objective: to determine if the combined treatment of the ATMP, hBM-MSC + biomaterial (G2), is superior to the control, iliac crest autologous graft (G1), to obtain radiological and clinical bone consolidation	Bone consolidation is considered achieved when meeting the three following criteria: (1) Radiographic bone bridging: new bone formation across the fracture site visible in 3/4 cortices, on at least 3/4 views (2) Clinical healing: pain less than 3 in a NRS (0 to 10) for pain during full weight bearing and without weight bearing [36] (3) No further surgical major intervention (nail replacement, plate replacement, or replacement of all components of the previous surgery)	At 12 months after surgery	Superiority (target delta of 20%). Percentages will be estimated using a log-binomial regression model including the treatment, manufacturing site, and baseline value of the REBORNE scale as covariates. If unexpectedly the model does not fit, the Poisson long-link distribution function with a robust variance estimator will be used instead.

SO1: to determine if the low dose of hBM-MSC + biomaterial (G2b) is noninferior to high dose of hBM-MSC + biomaterial (G2a) to obtain radiological consolidation	Score calculated in xR images from REBORNE radiological scale following the formula: REBORNE score = ∑(internal, external, anterior, and posterior cortical value^∗^)/(4 × number of evaluable cortices)	At 12 months after surgery	Noninferiority (target delta of 10%). A log-transformed data of the values will be used in a mix model for repeated measurements, only if the primary outcome reaches statistical significance. Differences between arms will be estimated through adjusted means, standard errors, and its 95% CI

SO2: to compare the percentage of bone consolidation between G1 versus G2 and G2a versus G2b treatment arms	As defined in the principal objective	(i) G1/G2: at 6 and 24 months after surgery (ii) G2a/G2b: at 6, 12, and 24 months after surgery	Fisher's exact test

SO3: to compare the radiological consolidation between G1 versus G2 and G2a versus G2b treatment arms	As defined in SO1	At baseline and 6, 12, and 24 months after surgery	*t*-test or Mann–Whitney test

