SO: secondary objective; NRS: Numeric Rating Scale; AE: adverse event. ^∗^Cortical value: 1 point if fracture is unchanged, 2 points if callus is noncontinuous, 3 points if callus is continuous but fracture is still apparent, 4 points if callus is with same density as cortical, and 0 points if noninterpretable or nonvisible. ^∗∗^Variables of interest: manufacturing centre (nominal), anatomical site of the fracture (femur, humerus, and tibia), sex (male, female), smoking habit (yes, no), and time since acute fracture (months).

**Table 2 tab2:** ORTHOUNION clinical trial inclusion/exclusion criteria.

*Inclusion criteria*
(1) Age 18 to 65, both sexes (2) Traumatic isolated closed or open Gustilo I and II, IIIA and IIIB humerus, tibial or femur diaphyseal, or metaphysodiaphyseal fracture with a status of atrophic, oligotrophic, or normotrophic nonunion. A nonunion is defined as a fracture not healed at least 9 months after the originating trauma that meets the following criteria: (i) Insufficient bone bridging to stabilize the fracture (ii) Insufficient bone biological activity in the fracture (iii) Failure of previous treatment (including bone grafting) (3) At least 9 months from acute fracture (4) Able to understand, accept, and sign informed consent (5) Medical health coverage (6) Able to understand and accept the study constraints
*Exclusion criteria*

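### The primary model leaves out anatomical site: the test stays valid, but some precision and protection against chance imbalance are given up

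*Protocol article*

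**What the plan says.** The principal-objective row of Table 1 fixes the primary analysis: "Percentages will be estimated using a log-binomial regression model including the treatment, manufacturing site, and baseline value of the REBORNE scale as covariates". If that model does not fit, a Poisson model with log link and robust variance replaces it.

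Anatomical site appears in three other places:

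- Section 3.2 declares it as a subgroup: "anatomical site: femur, humerus, and tibia".
- The Table 1 footnote lists it among the variables for the SO8 factor analysis: "anatomical site of the fracture (femur, humerus, and tibia").
- The Discussion, on the expected autograft healing rate, adds the caveat "although it may vary depending on the type and location of the nonunion".

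The bone is part of inclusion criterion 2 (Table 2), so it is known for every patient before randomisation. The only stratification factor the article names is production centre (Discussion), which the primary model already covers through manufacturing site.

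For the design, Section 3.1.1 sets 36 v 72 patients and says that "the control arm (G1) may have a rate of 74% in efficacy" and that "it is reasonable to expect 20% superiority for the rate of responders in the experimental arm (G2a + G2b"). The sample size is said to "achieve more than 80% power to detect superiority with a clinically meaningful margin of superiority of 20%, considering a 5% loss", and "The significance level of the test will be established at the 2.5% one-sided alpha level".

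**The concern.** A baseline factor that may predict the outcome, is already collected and is not balanced by design is a natural covariate. With 36 autograft patients, chance differences in the femur/tibia/humerus mix can be sizeable. If one bone heals less often, such a difference carries into the treatment contrast. An excess of the slower bone in the autograft arm favours the cells, and an excess in the cell arms hides a true gain.

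The endpoint gives a further reason to expect a location effect. It requires a low pain score during full weight bearing, which may mean something different for a humerus than for a leg bone. The baseline REBORNE score is purely radiographic and would not register that.

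The subgroup tests and SO8 look at location, but neither adjusts the primary estimate. At stake are a few points of power in a trial with little to spare, and how far an imbalanced result can be trusted.

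**Working it through.** **1. The plan's own power.** Inputs (Section 3.1.1): 36 v 72, 74% v 94% (the 20% read as an absolute difference), one-sided 2.5%.

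- Pooled rate: (36 × 0.74 + 72 × 0.94)/108 = 0.8733.
- Null SE: √[0.8733 × 0.1267 × (1/36 + 1/72)] = 0.0679.
- Alternative SE: √(0.74 × 0.26/36 + 0.94 × 0.06/72) = 0.0783.
- Power: Φ[(0.20 − 1.96 × 0.0679)/0.0783] = 80.4%.

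The stated figure is reproduced. With 5% loss (34.2 v 68.4) it is 78.5%. With the unpooled variance it is 72.4%, which is close to what the robust-Poisson test gives below.

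**2. How often a large imbalance arises.** Assume 50% tibia, 35% femur and 15% humerus (not in the article). The SD of the difference in tibia share is √[0.5 × 0.5 × (1/36 + 1/72)] = 0.102. A gap of at least 15 points in a given direction has probability 1 − Φ(0.15/0.102) ≈ 7%. Simulation gives about 8%.

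**3. What it does to the estimate.** Assume autograft success of 65/80/90% in tibia/femur/humerus (weighted mean 74%).

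- Non-tibia mean: (0.35 × 80 + 0.15 × 90)/0.50 = 83%, a gap of 18 points to tibia.
- With no treatment effect, a 15-point excess of tibias in G1 moves the G2 − G1 difference by 0.15 × 18 = 2.7 points.
- Null SE of the difference: √[0.74 × 0.26 × (1/36 + 1/72)] = 9.0 points, so the shift is 0.30 SE.
- An unadjusted normal test then has one-sided error 1 − Φ(1.96 − 0.30) ≈ 4.8%.

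**4. Simulation, 36 v 72.** Same mix and autograft rates; cell arms 90/97/99% (mean 94%). Each cell is without v with location.

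| Test | Overall power | Overall one-sided error | Error, G1 tibia excess ≥ 15 points | Power, G1 tibia deficit ≥ 15 points |
|---|---|---|---|---|
| Robust Poisson with five sites and baseline score (8,000 trials) | gain within the range below | 1.5–1.9% v at most 2.3% (all scenarios) | 3.3% v 1.2% | 59% v 73% |
| Pooled test v Cochran-Mantel-Haenszel (300,000 trials) | 81.1% v 82.2% | 2.6% v 2.7% | 5.9% v 2.4% | 70.4% v 80.7% |
| Logistic likelihood ratio with planned covariates (4,000 trials) | 79.7% v 81.1% | not run | 4.9% v 2.6% | 67.6% v 77.9% |

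Only the first row uses a model the article names. With no location effect it gives 71.6% v 71.9% power, so nothing is lost. With location effects the gain is about 1 to 3.5 points. About 8% of 8,000 is 640 trials, so the 3.3% has a simulation SE of √(0.033 × 0.967/640) = 0.7 points and the 59% one of √(0.59 × 0.41/640) = 1.9 points.

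**5. A second set of assumptions.** Femur/tibia/humerus 35/45/20%, robust Poisson with five sites but no baseline score, 6,000 trials per scenario:

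- Power without v with location: 72.1% v 72.4% (no effect), 70.8% v 71.9% (10-point spread), 71.3% v 74.3% (22-point spread).
- Overall error: 1.5–2.0% v 1.6–2.1%.
- In a separate run without the manufacturing-site terms, given a 19-point tibia excess in G1 (probability about 3%), error was 2.5% v 1.6% (10-point spread) or 3.4% v 1.4% (22-point spread).

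**6. Room in the model.** Expected failures are 36 × 0.26 + 72 × 0.06 = 13.7. The planned model has 1 (treatment) + 4 (five manufacturing sites) + 1 (baseline score) = 6 non-intercept parameters. Anatomical site makes 8.

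**The case against.** A reader might infer that the superiority test is distorted or that its error rate is inflated. The documents do not support that. Under randomisation the 2.5% already averages over chance imbalances. In the pooled-test simulation, 5.9% error when G1 has the tibia excess is offset by 0.9% in the mirror-image trials, and the overall rate is 2.6%. The 5 to 6% figures also come from tests the article does not plan.

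A reader might also take the Discussion to say that location affects healing. It says only that the rate may vary, gives no size, and says so as a caveat on the sample-size estimate. The location mix and every location-specific rate above are assumptions. Nor does the article give baseline REBORNE scores by bone, so it cannot be claimed that the score is equally low in all of them. These points stand.

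Two further objections stand in part:

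- **Sparse data.** With about 14 failures, two more parameters strain a log-binomial fit, and under the assumed rates the humerus group has no failures in 52% of trials. A plain iterative fit failed or gave inadmissible values in 97% of 300 simulated trials with the planned covariates and in over 99% with location. Those rates depend on the algorithm and show direction only. The fallback copes: it models success on the log scale, where a group with no failures still has a finite value, and its overall error stayed at or below 2.3%.
- **Why this factor?** Sex, smoking and time since fracture are listed beside location in Section 3.2. But of these, location is the one the Discussion names as a possible source of variation in the autograft rate.

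That the plan is coherent, with its stratification factor in the model, is true. It does not remove the gain on offer. The covariate list is a choice the article fixes, not a detail left to an unseen SAP.

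**Conclusion.** The point holds as a worthwhile improvement, not as an error or contradiction. Without location the primary test keeps its overall one-sided error. What is given up is about 0 to 3.5 points of power, and reliability in the roughly 7 to 8% of trials in each direction with a tibia imbalance of 15 points or more. Under the 65/80/90% gradient and the robust-Poisson fallback, error is then about 3.3% v 1.2%, and power in the opposite case about 59% v 73%, without v with location. All of this depends on assumed mixes and rates. If location has little effect, the omission costs nothing, and including it costs almost nothing under the fallback.

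**What to change.** In the principal-objective row of Table 1, and in the SAP, add anatomical site with three levels (femur, tibia, humerus) to treatment, manufacturing site and baseline REBORNE score. Keep the stated robust-Poisson fallback. Fix this before outcomes are compared by arm, and apply it whatever imbalance is seen; adding location only after an imbalance has appeared would not be credible.

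Do not collapse to upper versus lower limb to save a parameter. That merges tibia with femur, the contrast that matters most here. In the pooled-test simulation it lowered the conditional error only from 5.9% to 4.8%, against 2.4% with three levels.

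The cost is one line of text, with no new data and no extra patients. The downside is two more parameters (8 instead of 6) for about 14 expected failures, so the log-binomial model may fail to converge more often and the fallback may be used more often.

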## 2. Material and Methods

### 2.1. Trial Characteristics and Design

ORTHOUNION is a multicentre, open, comparative, randomized, clinical trial with three parallel arms to evaluate the efficacy at one and two years of two doses of an ATMP against iliac bone autograft to enhance bone healing in patients with long bone nonunion (EudraCT number 2015-000431-32). A total of 108 patients will be randomly assigned to either the experimental low-dose arm, experimental high-dose arm, or the active comparator arm (ICA) with a 1 : 1 : 1 allocation using a central randomization service. The experimental low dose contains a total number of 100 × 10^6^ hBM-MSCs suspended in 5% human albumin up to a total volume of 10 mL (cell concentration of 10 × 10^6^). The experimental high dose contains a total number of 200 × 10^6^ hBM-MSCs suspended in 5% human albumin up to a total volume of 10 mL (cell concentration of 20 × 10^6^). Each experimental dose will be combined with 10 cc of the granulated biomaterial MBCP+ (Biomatlante, Nantes, France). The trial will be conducted in 20 clinical investigational sites in four European countries (France, Germany, Italy, and Spain) under the same clinical protocol and standardized surgical techniques. The cell product derived from autologous hBM-MSCs will be expanded in 4 different GMP manufacturing facilities in France (EFS Ile de France, Centre de Thérapie Cellulaire de Créteil), Germany (Institut für Klinische Transfusionsmedizin und Immungenetik Ulm Gemeinnützige GmbH (IKT Ulm), DRK-Blutspendedienst Baden-Würrtemberg–Hessen und Universitätsklinikum Ulm, Ulm), Italy (Fondazione IRCCS Ca' Granda Ospedale Maggiore Policlinico, Cell Factory “F. Calori”, Milano), and Spain (Unidad de Producción Celular UPC, Hospital Puerta de Hierro-Majadahonda, Universidad Autónoma de Madrid, Servicio de Hematología y Hemoterapia, Madrid).

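### At the trial's own planning rates the log-binomial primary model will usually fail to fit, and its Poisson fallback, read with a Wald test, has about 10 points less power than the test that reproduces the stated figure

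*Protocol article*

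**What the plan says.** For the principal objective, Table 1 states: "Percentages will be estimated using a log-binomial regression model including the treatment, manufacturing site, and baseline value of the REBORNE scale as covariates". It then provides for a substitute: "If unexpectedly the model does not fit, the Poisson long-link distribution function with a robust variance estimator will be used instead" (evidently a log link is meant). The same cell gives a 20% delta as the superiority target.

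Section 3.1.1 plans one control patient for every two experimental patients. It states that "the sample size of 36 in comparator arm (ICA) and 72 in experimental arm (hBM-MSC) achieve more than 80% power", with 5% loss allowed for and a one-sided 2.5% level. On the control rate it says that "the control arm (G1) may have a rate of 74% in efficacy". On the gain in G2 its view is that "it is reasonable to expect 20% superiority for the rate of responders in the experimental arm".

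Section 3.2 counts patients with unknown consolidation as failures. It lists the site factor as "manufacturing site (Spain, France S1, France S2, Germany, and Italy", whereas section 2.1 says the cells "will be expanded in 4 different GMP manufacturing facilities in France", Germany, Italy and Spain, with one facility named in each country.

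**The concern.** A log link is valid only if every fitted probability stays below 1. When nearly all treated patients are expected to heal, and several site terms and a continuous score are added in 108 patients, the maximum of the likelihood tends to sit on that limit and ordinary fitting fails. The plan treats this as a surprise. If it is the usual outcome, the fallback is the real primary analysis, and the stated power should describe the fallback.

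Both models give a relative risk as the treatment coefficient, while the trial is sized on a difference of 20 percentage points. A Wald test on the log-relative-risk scale is conservative when success is common. The trial could therefore miss its planned effect more often than the sample-size section says.

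**Working it through.** **Inputs.** From section 3.1.1: n1 = 36, n2 = 72, p1 = 0.74, one-sided alpha 0.025 (z = 1.96), 5% loss. The G2 rate p2 = 0.94 is inferred as 74% plus 20 points; it is not printed, but it reproduces the stated power. Model terms are from Table 1 and the missing-as-failure rule from section 3.2. Site balance and the baseline REBORNE distribution are not given, so they were assumed and varied.

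**1. The stated power.** For the pooled test of a difference, power = Φ[(p2 − p1 − 1.96·SE0)/SE1].
- Pooled rate = (36×0.74 + 72×0.94)/108 = 0.8733.
- SE0 = √[0.8733×0.1267×(1/36 + 1/72)] = 0.0679.
- SE1 = √[0.74×0.26/36 + 0.94×0.06/72] = 0.0783.
- Power = Φ[(0.20 − 0.1331)/0.0783] = Φ(0.855) = 80.4% (82.0% by exact enumeration).

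With 34 and 68 patients after 5% loss it is 78.3% (exact 79.4%). The stated figure is reproduced to within about 2 points.

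**2. The same data on the log-relative-risk scale, unadjusted Wald test.**
- ln(0.94/0.74) = 0.2392.
- SE = √[0.26/(0.74×36) + 0.06/(0.94×72)] = 0.1032.
- Power = Φ(0.2392/0.1032 − 1.96) = Φ(0.359) = 64.0% (exact 69.8%).

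Without covariates this variance is the same for the log-binomial and the robust Poisson model, so their Wald tests agree. For comparison, a Wald test on the unpooled difference has exact power 74.8%, and a likelihood-ratio test in the unadjusted log-binomial model about 82%.

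**3. Does the log-binomial model fit?** Expected failures are 36×0.26 = 9.4 in G1 and 72×0.06 = 4.3 in G2, about 14 in all. The model has 6 coefficients (four sites) or 7 (five sites). Share of simulated trials at 74% versus 94% with a maximum inside the permitted range:
- treatment only: 98.9%
- plus baseline score: 49%
- plus four sites and baseline: 3–4%
- plus five sites and baseline: 1–1.5%, falling to 0.5% if baseline is prognostic.

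Ordinary iterative fitting reached a valid solution in 3–9% of trials with site and baseline in the model. With losses as failures the rates become 0.74×0.95 = 70.3% and 0.94×0.95 = 89.3%; an interior maximum then exists in 6–17%. It is commoner at lower success: 37% at 60% versus 80%, and 37–57%, depending on the set-up, when both arms are at 74%.

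**4. Power of the fallback.** Log-link Poisson with robust Wald test and the same covariates, at 74% versus 94%:
- 36/72: 67–75% across set-ups; where the pooled difference test was run on the same data, it had 81–85% and the gap was 9–12 points.
- 34/68: 67% against 79%.
- 36/72 with losses as failures: 56–60%, against about 70% for the pooled test.

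The last line has two causes. Counting losses as failures takes the pooled test itself from about 82% to about 70%; the choice of test takes the rest.

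**5. One-sided error of the fallback.** About 1.2–1.9% in runs of 2,500 to 8,000 null trials. One run of 1,000 gave 2.7%, with a simulation standard error of 0.5 points.

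**6. Site levels.** Section 2.1 names four facilities, one of them in France. Section 3.2 lists five sites, two of them in France. The factor is a term in the primary model, and the fifth level makes fitting harder (step 3).

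**The case against.** Several points against the concern are sound.

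- A reader might infer that the switch to Poisson is what costs power. It is not: the log-binomial Wald test has essentially the same power (69.8% exact, against 70.6% for robust Poisson in simulation, both unadjusted). The loss belongs to the scale and the Wald form, measured against the pooled difference test.
- The article names no test statistic. Wald is the usual companion of a robust variance but is inferred here, and a likelihood-ratio test in a log-binomial model that did fit would lose little.
- A reader might infer that the primary result is picked from the data or may not exist. The fallback is prespecified, is triggered by non-fit and not by the treatment result, and has the same null: a relative risk of 1 is a difference of 0. An analysis always exists and error is not inflated.
- A relative-risk model does not contradict a 20-point design target. Arm percentages can be estimated from it, and a journal article need not state every interval scale.
- It would be too strong to say the model almost never fits. That holds at the planning rates with no loss and weakens as success falls. The Discussion (section 4) itself warns that small changes in the rates affect power.

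What remains is that Table 1 calls the expected outcome unexpected, and that section 3.1.1 states a power which the analysis likely to be run does not deliver. Both are written in the article, so neither is detail left to an unseen analysis plan.

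**Conclusion.** The concern holds in this limited form. At the planning rates the named model lacks an interior maximum in 96% or more of trials (83–94% with losses as failures), so the fallback is the likely primary analysis. With a Wald test its power is about 67–75%, or 56–60% with losses as failures. The shortfall against the pooled difference test is 9–12 points in the first case and somewhat more in the second. The direction is conservative: the risk is a missed effect, with no sign of a false claim of superiority.

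The conclusion rests on the inferred 94%, the assumed Wald test, and assumed site sizes and baseline distribution. Non-fit at the planning rates was stable over equal and unequal sites and over discrete and continuous baseline scores. The four-versus-five site mismatch is a separate, minor inconsistency.

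**What to change.** Replace the model and its fit-dependent switch with one prespecified primary analysis that fits at high success rates. Logistic regression with the same covariates is one candidate: report the standardised risk difference with a 95% confidence interval, on the scale of the 20-point target, and the relative risk as secondary.

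Name the test and derive the interval so that the two agree. This matters: in simulation the logistic likelihood-ratio test had 80–82% power, while a Wald interval for the standardised difference excluded zero in only 76–78% of trials. Check the one-sided error by simulation as well. The likelihood-ratio test ran at about 2.3–3.1%, so part of its gain is liberal error and a small-sample correction may be needed.

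Restate the power for the chosen test with losses counted as failures. Use the production-centre stratum from randomisation (section 4) as the site term in all arms, and reconcile sections 2.1 and 3.2 on its number of levels.

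The cost is analysis wording, standard software and a modest simulation. The downsides are a model-standardised main estimate and possibly a less favourable stated power.
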